# MAGIC (maternal glucose in pregnancy) understanding the glycemic profile of pregnancy, intensive CGM glucose profiling and its relationship to fetal growth: an observational study protocol

**DOI:** 10.1186/s12884-023-05824-x

**Published:** 2023-08-03

**Keywords:** Gestational diabetes, Continuous glucose monitoring, Glycemia, Pregnancy, Fetal growth, Large for gestational age, Early diagnosis

## Abstract

**Background:**

Continuous glucose monitoring (CGM) provides the most objective method of assessing glucose in daily life. Although there have been small, short-term physiologic studies of glucose metabolism in ‘healthy’ pregnant women a comprehensive, longitudinal description of changes in glucose over the course of pregnancy and how glucose dysregulation earlier in pregnancy relates to traditional third trimester screening for gestational diabetes, fetal growth and pregnancy outcomes is lacking. This study aims to characterise longitudinal changes in glycemia across gestation using CGM, in order to understand the evolution of dysglycemia and its relationship to fetal growth.

**Method/design:**

A multi-centre, prospective, observational, cohort study of 500 healthy pregnant women, recruited in the first trimester of pregnancy. Masked CGM will be performed for a 14-day period on five occasions across pregnancy at ~ 10–12, 18–20, 26–28, 34–36 weeks gestation and postnatally. Routinely collected anthropometric and sociodemographic information will be recorded at each visit including: weight, height, blood pressure, current medication. Age, parity, ethnicity, smoking will be recorded. Blood samples will be taken at each visit for HbA1c and a sample stored. Details on fetal growth from ultrasound scans and the OGTT results will be recorded. Maternal and neonatal outcomes will be collected. CGM glucose profiling is the exposure of interest, and will be performed using standard summary statistics, functional data analysis and glucotyping. The primary maternal outcome is clinical diagnosis of GDM. The primary neonatal outcome is large for gestational age (LGA) (> 90th centile defined by customised birthweight centile). The relationship of glucose to key secondary maternal and neonatal outcomes will be explored.

**Discussion:**

This study will ascertain the relationship of maternal dysglycemia to fetal growth and outcomes. It will explore whether CGM glucose profiling can detect GDM before the OGTT; or indeed whether CGM glucose profiling may be more useful than the OGTT at detecting LGA and other perinatal outcomes.

**Trial registration:**

ISRCTN 15,706,303 https://www.isrctn.com/ISRCTN15706303 Registration date: 13th March 2023.

## Background

The UK has one of the highest rates of stillbirth and neonatal death in Europe [1]. The MBRRACE-UK report identified that half of mothers with a perinatal death had an abnormality of fetal growth [1]. Furthermore, infants who are born large or small for gestational age (LGA or SGA respectively) are predisposed to developing obesity and Type 2 Diabetes (T2DM) perpetuating an intergenerational cycle of cardiometabolic disease [2–4].

Amongst the many factors that influence fetal growth, maternal glycemic control plays a key role and is a modifiable risk factor. Maternal hyperglycaemic excursions stimulate fetal insulin secretion leading to increased fetal adiposity and growth [5]. This increases the risk of preterm and instrumental delivery, neonatal hypoglycaemia requiring neonatal intensive care unit (NICU) admission, caesarean section, stillbirth. Difficulties at delivery can lead to brain damage, shoulder dystocia and permanent disability [6, 7]. Observational studies demonstrate that varying degrees of dysglycemia during pregnancy, including pre-existing diabetes and gestational diabetes (GDM) are associated with LGA related adverse perinatal outcomes [8, 9].

To mitigate against hyperglycemia related fetal growth and associated adverse pregnancy outcome, clinical guidelines currently recommend testing for pregnancy related dysglycemia at 24–28 weeks gestation by an oral glucose tolerance test (OGTT) [10]. NICE recommends diagnosis of GDM on the basis of a raised fasting or 2 h glucose. This late pregnancy diagnosis of GDM is an increasing cause for concern; we have shown that excess fetal growth assessed by ultrasound scan is detectable from 20 weeks’ gestation, pre-dating biochemical diagnosis of GDM [11, 12]. Whilst we now know that testing at 24–28 weeks gestation is too late to prevent abnormal fetal growth, there is no validated test for earlier diagnosis and the optimal time of screening and treatment for dysglycemia remains unknown [13]. Indeed, despite OGTT testing, the majority of LGA babies are born to mothers without a diagnosis of GDM [8, 14, 15]. This concurs with the recognition that the OGTT is insufficiently sensitive and that many women who could benefit from treatment will not be correctly identified, contributing to the failure to improve outcomes. The OGTT, recognised to be an outdated test for diabetes diagnosis, is now used only in pregnancy. It is known to be poorly reproducible: 40% of pregnant women who had a 2nd OGTT immediately after an abnormal OGTT had normal results and vice-versa [16].

Glucose control is dynamic, with glucose tolerance and insulin sensitivity varying across the 24 h day with a circadian rhythm [17, 18]. Insulin sensitivity also varies across pregnancy, with insulin resistance increasing with gestation [19]. As the OGTT relies on just two glucose readings taken two hours apart on one day, it cannot detect the nuances of daily glycemic variations, or changes across pregnancy.

Continuous glucose monitoring (CGM) provides the most objective method of assessing glucose in daily life [20]. With up to 288 interstitial fluid glucose measurements per day and > 4000 measures over a single 2-week sensor life-span, CGM accurately reflects blood glucose variations [20]. Although there have been small, short-term physiologic studies of glucose metabolism in ‘healthy’ pregnant women [19, 21–23] a comprehensive, longitudinal description of changes in glucose over the course of pregnancy and how glucose dysregulation earlier in pregnancy relates to traditional 3rd trimester GDM screening, fetal growth and pregnancy outcomes is lacking. The availability of non-burdensome, CGM technology and intensive glucose profiling techniques provides a new opportunity to accomplish this goal.

Building on our earlier work [24–31] we hypothesise that intensive glucose profiling of CGM will be able to detect maternal glucose dysregulation early in pregnancy that current clinical testing does not detect and that this will be associated closely with the development of LGA and adverse pregnancy outcomes.

## Methods / design

### Primary research questions

To characterise longitudinal changes in glycemia across gestation and into the postnatal period, by obtaining detailed CGM glucose summary statistics, functional data analysis profiles and glucotype at multiple time points.To determine the relationship between CGM glucose measures, fetal growth and pregnancy outcomes.To determine the relationship of the CGM glucose measures to the OGTT and HbA1c.

#### Study design

A multi-centre, prospective observational cohort study.

#### Population

500 healthy pregnant women in the first trimester of pregnancy.

#### Eligibility criteria

Women aged 18–45 years with a singleton pregnancy who are classified as at risk for GDM with at least 1 of the following risk factors: BMI > 30 kg/m2; previous unexplained still birth or baby > 4.5 kg; first degree relative with diabetes; ethnic minority group (e.g. South Asian, Middle-Eastern, Afro-Caribbean).

#### Exclusion criteria

Women presenting beyond 14 weeks gestation; T1DM or T2DM; previous GDM; women on metformin therapy for infertility; multiple pregnancy, fetal congenital abnormality; significant co-existent medical or psychiatric conditions; unable to understand English and no translator available.

#### Recruitment

Participants will be recruited from three major Hyperglycemia in Pregnancy NHS services across the UK. Pregnant women will be invited to participate in the study at their routine clinical dating scan (10–12 weeks), having been sent written information about the study prior to this.

#### Study visits and data collection

Those who consent to take part will wear CGM for a fortnight on five occasions at ~ 10–12, 18–20, 26–28, 34–36 weeks gestation and immediately postnatally (to coincide with routine clinic attendance to minimise burden and to maximise participation/concordance where possible), see Table 1.

**Table 1 Tab1:** Spirit table

Summary of information collected		Visit 1	Visit 2	Visit 3	Visit 4	Visit 5
**Gestation (weeks)**		10–12	18–20	26–28	34–36	Immediate postnatal
**Enrollment**	Eigibility screen	x				
	**Consent**	x				
**Maternal**	Demographics	x				
	BMI	x	x	x	x	x
	BP	x	x	x	x	x
	Pregnancy outcome and complications					x
**Laboratory**	OGTT			x		
	HbA1c	x	x	x	x	x
	Blood stored	x	x	x	x	x
	Rectal swab			x		
	Placenta and cord blood stored					x
**CGM (2 weeks)**		x	x	x	x	x
**Neonatal**	Birthweight					x
	Anthropometry					x

Routinely collected anthropometric and sociodemographic information will be recorded at each visit including: weight, height, blood pressure, current medication. Age, parity, ethnicity, smoking will be recorded at the first visit. Blood samples will be taken at each visit for HbA1c and a sample stored (for subsequent analysis to identify mechanisms underlying dysglycemia, as well as predictors of GDM and fetal growth). The research midwife will insert the CGM sensor and the participant will return it via stamped addressed envelope for data download. Details on fetal growth from ultrasound scans (USS) and the OGTT results will be recorded. A rectal swab will be requested (optional) at 26–28 weeks gestation and stored for microbiome analysis.

Post-delivery, placenta and cord blood samples will be collected and stored in designated Human Tissue Act approved and compliant facilities for later analysis. Infant anthropometry measures will be taken (skin fold thickness). Maternal and neonatal outcomes will be collected as detailed below.

##### CGM measurement

A small factory calibrated, masked (patient cannot see the data) CGM device, (Abbott Diabetes Care) will be used. It is a small discreet, water resistant sensor, with a very thin filament (< 0.4 mm thick) that is inserted (painlessly) 5 mm beneath the skin surface on the upper arm. It is factory calibrated, making it far more convenient and removing the risk for sensor inaccuracies from calibration user error (capillary meter inaccuracy, not washing hands etc.) seen with other CGM devices. A single reader device (at each centre) is used to activate and retrieve the data. The accuracy and safety of this device has been established in pregnant women across all trimesters, including those with HbA1c levels indicating euglycaemia [32] The accuracy has been established across the full range of glucose levels likely to be observed in this study, including those in the normal glucose range. Importantly, it is extremely acceptable to pregnant women and is CE marked and fully approved for use in pregnancy [32].

##### CGM glucose profiling

Standard summary statistics of the CGM data for each of the five measurement periods will be calculated, including: mean daily/weekly CGM glucose; percentage of time spent within, above, and below the glucose target range of 3.5–7.8 mmol/l; area under the curve (a measure of participants’ exposure to high, low and normal glucose levels over time) for all glucose measurements that exceed thresholds of 7.8 mmol/l or 6.7 mmol/l, and fall below thresholds of 3.5 mmol/l or 2.8 mmol/l; number of high/low glucose excursions; glycaemic variability [20]. Functional data analysis will be performed as previously detailed to generate temporal profiles for each measurement period [24, 29–31]. Glucotyping will be performed as previously described [33].

##### Other glucose measures

The blood glucose values obtained in response to 75 g OGTT at 24–28 weeks’ gestation will be recorded at 0 and 120 min. HbA1c will be analysed to DCCT standards.

##### Assessment of fetal growth

Infant birthweight will be recorded. LGA will be defined as birthweight > 90th centile and SGA < 10th centile, using customised GROW birthweight centiles, ([contact]) which adjusts for maternal height, weight, ethnicity, parity, neonatal sex and gestational age. Fetal anthopometry measures, including sum of skin folds and neonatal fat mass, will be taken after delivery. USS are performed routinely in all pregnant women at 12 weeks (dating scan) and 20 weeks (anatomy scan) gestation and in women diagnosed with GDM growth scans are performed at 28, 32 and 36 weeks gestation [10]. Fetal biometry and estimated fetal weight will be obtained from each.

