### Secondary outcomes

Secondary outcomes include other measures of fetal growth (to include: birthweight; SGA on GROW centile; LGA and SGA defined on Intergrowth and WHO centiles; neonatal adiposity at birth; USS measures of abdominal circumference, estimated fetal weight at 28, 32 and 36 weeks gestation) and the range of maternal and neonatal outcomes as above.

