### Statistical analysis plan

A Directed Acyclic Graph will be developed to direct the modelling of the data to correctly identify confounders, mediators and competing exposures [34].

Detailed CGM glucose summary statistics, functional data analysis profiles and glucotype will be generated for both weeks of each of the five measurement periods (a minimum of 96 h CGM data at each visit will be needed to be included in the analysis). Means ± SD values or percentiles appropriate to the variable under consideration will be reported for the covariates in relation to the outcome. Primary analysis will initially retain the measures of glucose (as the primary exposure of interest) distinct at different time of gestation. The modelling will adjust for week of gestation, and is already adjusted for maternal height, weight, ethnicity, parity, neonatal sex using the GROW centile. Selected CGM outcomes will also be calculated to compare the between group differences. For assessing group differences in secondary outcomes of fetal growth measures and maternal and neonatal outcomes, regression models will be used to compare continuous and ordinal variables, logistic regression will be used to compare categorical variables, and Poisson regression models will be used to compare event rates. Missing data for outcomes will not be imputed. Available case analysis method will be used for secondary outcome analyses in each time point.

Functional Data Analysis: The life course nature of the data means that, for any individual, the measures will be more correlated than those measures between individuals. A functional multilevel model will be used to reflect the complex structure of the data, as well as covariance and correlations therein, to correctly infer statistical relevance within the model. Point estimates, 95% confidence intervals and p-values will be reported for the average effect at each time point of CGM measurement. Residual values will be examined for an approximate normal distribution. If values are highly skewed then a transformation or robust statistical methods will be used instead.

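### Ultrasound outcomes at 28, 32 and 36 weeks are listed for the whole study, but those scans are scheduled only for women diagnosed with GDM

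*Protocol article*

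**What the plan says.** All of this is in the protocol article.

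- **Assessment of fetal growth**, scans for everyone: "USS are performed routinely in all pregnant women at 12 weeks (dating scan) and 20 weeks (anatomy scan) gestation". Later scans: "in women diagnosed with GDM growth scans are performed at 28, 32 and 36 weeks gestation". Use of the scans: "Fetal biometry and estimated fetal weight will be obtained from each".
- **Study visits and data collection**: Table 1 has no research ultrasound. The text says that fetal growth details from scans will be recorded.
- **Secondary outcomes**: the list includes "USS measures of abdominal circumference, estimated fetal weight at 28, 32 and 36 weeks gestation", with no restriction to women with GDM.
- **Statistical analysis plan**: "Available case analysis method will be used for secondary outcome analyses in each time point", and "Missing data for outcomes will not be imputed".
- **Primary research questions**: "To determine the relationship between CGM glucose measures, fetal growth and pregnancy outcomes", posed for the cohort.
- **Primary outcome**: a clinical diagnosis of GDM is the primary maternal outcome.
- **Sample size estimation**: GDM prevalence is put at 10%, drop-out at about 30%, recruitment at 500.
- **Background**: "excess fetal growth assessed by ultrasound scan is detectable from 20 weeks", ahead of the biochemical diagnosis of GDM.

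**The concern.** The outcome list and the scan schedule do not match. The late ultrasound outcomes are stated for the study as a whole, yet the article provides no scan to supply them in women without GDM. Whether a woman has a value depends on the primary maternal outcome, which is diagnosed from glucose, the same domain as the exposure. The gap is structural, and an available-case rule does not repair it; it simply analyses whoever was scanned.

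Followed as written, the late ultrasound analyses would describe glucose and growth among women with GDM while standing under a question about the whole cohort. The Background says that most LGA babies are born to mothers without a GDM diagnosis, and those are the women with no scheduled late scan. The analysis section also plans group comparisons of fetal growth measures. If the groups are GDM and no GDM, the scheduled scans give no comparison group. The Discussion intends the data to inform screening guidelines, so the label on such a result matters.

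Meanwhile the 20-week scan, done in every woman and at the age the Background singles out, is not a named outcome.

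**Working it through.** **1. The plan's own figures (two-sided 5% assumed; the article does not state sidedness).**
- Mean glucose, 28 v 252, difference 0.4, SD 0.6: standard error = 0.6 × √(1/28 + 1/252) = 0.1195; 0.4/0.1195 − 1.96 = 1.387; power 91.7%.
- Glucotype, 38 v 346, 64% v 37%, no continuity correction: pooled proportion 0.397, standard error 0.0836 under the null and 0.0821 under the alternative; (0.27 − 1.96 × 0.0836)/0.0821 = 1.293; power 90.2%.

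Both agree with the stated 90%. The sample size is not in question here, and the 10% outcome prevalence is the planning figure behind it.

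**2. Women with a scheduled late scan.** Completers = 500 × (1 − 0.30) = 350. Count = prevalence × 350. Standard-error ratio against the whole cohort = √(350/count). The smallest correlation detectable at 90% power is r = tanh[(1.960 + 1.282)/√(n − 3)]; with all 350 women it is 0.17.

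| GDM prevalence | Women scanned | No scheduled value | SE ratio | Detectable r |
|---|---|---|---|---|
| 10% (plan) | 35 | 90% | √10 = 3.16 | 0.52 |
| 20% (assumed) | 70 | 80% | √5 = 2.24 | 0.38 |
| 30% (assumed) | 105 | 70% | √3.33 = 1.83 | 0.31 |

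With no drop-out, 10% of 500 is 50 women (r = 0.44). The 20% and 30% rows are there because the eligibility criteria require a GDM risk factor, so the rate could exceed 10%.

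**3. The 28-week scan.** The OGTT is at 24–28 weeks, and visit 3 at 26–28 weeks. A diagnosis near the end of that window may come too late for the 28-week scan, so that time point could be thinner still.

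**4. What the selection does (illustrative simulation).** Assumptions: true glucose–growth correlation 0.2 or 0.3; GDM is the top 10% of a score that correlates 0.5 to 0.9 with glucose; no effect of GDM care.
- The correlation inside the GDM subset falls to 0.12–0.18 (true 0.2) or 0.18–0.27 (true 0.3).
- Power with 35 women, from Φ[atanh(r)·√32 − 1.96], is 10–18% or about 18–36%, against 96.5% or more with all 350.
- The linear slope stays at 0.20–0.21 or 0.30–0.31, essentially unbiased.

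So selection on glucose alone costs precision and range. It does not by itself distort the slope.

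**5. Timing of CGM against the 20-week scan.** A 14-day sensor placed at 10–12 weeks ends at 12–14 weeks, before the scan. One placed at 18–20 weeks ends at 20–22 weeks, so its wear can overlap or follow the scan.

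**The case against.** The strongest reply is that this touches one item in a list of secondary outcomes. Both primary outcomes, birthweight, SGA, the alternative-centile outcomes and neonatal adiposity do not depend on a late scan, and the sample size does not rest on ultrasound. That stands. A reader might infer that the fetal-growth question as a whole is lost; the birth outcomes still address it in the full cohort.

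Other tempting inferences also go too far:

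- **That late scans exist only in women with GDM.** The article describes routine provision and does not rule out scans for other clinical reasons. None is promised, however, and women scanned that way would also be a selected group.
- **That the subset is treated and the slope therefore biased.** The article does not describe GDM treatment in this cohort. Bias would need an effect of GDM care or selection on growth-related factors. Either is possible; neither is shown.
- **That the 20-week measure is discarded.** Biometry is to be obtained from that scan, and the outcome list is introduced as non-exhaustive. The measure is simply not named.
- **That abdominal circumference is certainly confined to the late weeks.** The punctuation leaves some doubt, though that is the likely reading. Estimated fetal weight is clearly tied to them.

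One could also say that analysis sets belong to a SAP that is not shown, or that the promised directed acyclic graph will deal with conditioning on GDM. But the article itself states both the outcome and the scan schedule, and they disagree; a causal diagram cannot supply measurements in women who were not scanned.

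**Conclusion.** The point holds at moderate severity. As scheduled, the 28/32/36-week ultrasound outcomes come from a subset defined by the primary maternal outcome: about 35 of 350 women at the plan's 10% prevalence, with standard errors about 3.2 times those of the whole cohort, or 70–105 of 350 and about 2.2 to 1.8 times at an assumed 20–30%. Such an analysis is imprecise, covers a restricted glucose range and does not generalise to the cohort. Within women with GDM, and labelled so, it is limited rather than invalid.

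The counts rest on 30% drop-out, on every woman with GDM receiving the listed scans, and on no late scans in other women. How far the glucose range is restricted depends on how closely CGM glucose tracks the diagnosis, which the article does not quantify.

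**What to change.** In Secondary outcomes:

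- Name abdominal circumference and estimated fetal weight at the routine 20-week scan as the cohort-wide ultrasound outcome.
- Relate them to the 10–12 week CGM as the prior exposure. Report the 18–20 week CGM as a concurrent association only, because of the overlap in timing.
- State that the 28/32/36-week measures are descriptive within women with GDM and are not reported as cohort associations.

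The cost is wording in the outcome list and the matching analysis text; the 20-week biometry is already to be obtained. The downside is that the cohort-wide ultrasound outcome then sits earlier in gestation and says nothing about late fetal growth, for which the birth measures remain the whole-cohort evidence.

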##### Maternal and neonatal pregnancy outcomes

The following outcomes will be recorded: Maternal - hypertensive disorders (chronic; gestational; pre-eclampsia); mode of delivery inc. caesarean section; maternal weight gain; maternal length of stay; Neonatal - pregnancy loss < 20 weeks; stillbirth; termination; congenital anomaly; preterm births (< 37 weeks; <34 weeks) gestational age at delivery; neonatal hypoglycaemia, neonatal ICU admission, birth injury, shoulder dystocia, hyperbilirubinemia, respiratory distress; infant length of stay; composite neonatal outcome.

